### Examiners

Examiners will be manual therapists working at least 20 hours a week in their private practices in the Netherlands and registered by the Dutch Association for Manual Therapy or the Royal Dutch Society for Physical Therapy. From a database of those graduated from the Institute for Master Education in Musculoskeletal Therapy (SOMT: Stichting Opleidingen Musculoskeletale Therapie, Amersfoort, the Netherlands), 14 pairs of manual therapists will be invited to participate. Each pair works together in the same practice and practices will be selected based on their ability to logistically organise the study. We aim to include therapists who vary in years of clinical experience in manual therapy. Therapists will attend an information session followed by a two-hour training session in which procedures for digitally registering data are explained and practised. They will not receive additional training in history-taking, physical examination procedures, or using questionnaires. Pairs of therapists will be strictly requested not to discuss their experiences during the study with each other until their last patient has been included. Gender, age, years of clinical experience in manual therapy, highest diploma, practice setting, weekly amount of work related to spinal disorders (hours), teaching experience (yes/no), and participation in research (yes/no) will be recorded as professional characteristics from the participating therapists.

In each practice, a third colleague will function as a research assistant to coordinate the inclusion and flow of patients. Research assistants will be instructed with respect to applying the inclusion criteria, the order of assigning patients to therapists, and assuring blinding procedures.

### Procedures

From eligible patients, demographic (gender, age, marital status, working status) and clinical (type of complaints (neck or low-back pain), duration of complaints (days), radiation (yes/no), traumatic origin (yes/no), comorbidity (yes/no)) data will be recorded as baseline data by the local research assistant. In addition, baseline pain and disability will be determined using the Numeric Pain Rating Scale (NPRS 0–10, higher scores indicate higher pain intensity), and the Quebec Back Pain Disability Scale (QBPDS 0–100, higher scores indicate higher disability) for low-back pain patients and the Neck Disability Index Dutch Language Version (NDI-DLV 0–50, higher scores indicate higher pain and disability) for neck pain patients, respectively. The NPRS is a reliable and valid scale to measure pain intensity in adults
[60]. The Dutch version of the QBPDS is a reliable and valid instrument for measuring disability in low-back pain patients
[61] and the Dutch version of the NDI is recommended for measuring pain and disability in patients with neck pain
[62].

All baseline data will be available to each therapist before he or she starts the diagnostic process. The first therapist of each pair will be the treating therapist to whom the patient was assigned to, so the order in which both therapists act as the first examiner will vary according to the practice’s planning. The first therapist will screen all consecutive patients with neck or low-back pain for the presence of red flags
[63]. In accordance with guidelines in the Netherlands
[64], patients suspected of having serious (spinal or non-spinal) pathology will not enter the study which will be recorded. Patients will then undergo a full history-taking by the first therapist. The therapist will record his or her findings as well as proposed hypotheses about patient’s health status by formulating explicit objectives for further examination. The therapist will then choose the diagnostic procedures (e.g. observation, physical tests, performance tests, questionnaires) that he or she plans to perform in the patient. After performing each procedure, its outcome will be recorded. If PIVM assessment is indicated, therapists will use three-dimensional coupled movements in flexion and extension directions for each individual motion segment
[65]. Movements will be judged on mobility (hypermobile-normal-hypomobile), resistance perceived by the therapist during the movement (increased resistance or stiffness yes/no), resistance perceived by the therapist at the end of the movement (end-feel) (increased resistance or stiffness at the end of the movement yes/no), and pain provocation (yes/no). Therapists will perform a maximum of three repetitions for each movement per direction per spinal motion segment to afford the best stiffness discriminability
[66].

The therapist will then be asked to record whether he or she has made any changes to the original examination objectives as well as to specify these changes, and a diagnostic conclusion in terms of specific or non-specific neck or low-back pain is given. Finally, the therapist will make the decision about whether or not SMT is indicated in the patient and, when indicated, it will also be stated whether mobilisations or manipulations, or both, are indicated, and to which spinal motion segments these techniques would be targeted. In addition, the therapist will rate his or her level of certainty of the primary decision about the indication on a bipolar seven-point scale ranging from -3 (completely uncertain) to 3 (completely certain). It will also be recorded which other interventions he or she believes would further be indicated in the patient. However, at this point, no actual treatment will be provided.

After the first therapist has performed the full examination, he or she will leave the examination room and the patient will be given a 10 minute break. After checking whether all data have been registered, the research assistant then guides the second therapist into the room and makes sure that there is no visual or verbal contact between the two therapists. The second therapist will then conduct the full diagnostic process, excluding the screening for red flags, whilst being unaware of the outcomes of the first examination. Patients will be requested not to mention any outcomes or conclusions from the first examination. Both therapists will record all their findings and data into a fit-for-purpose software program. The research assistant will check whether all data have been entered by both therapists.

### Statistical analysis

Demographic and clinical baseline characteristics of patients will be summarised using descriptive statistics. Absolute and relative frequencies are used to describe categorical data. Ordinal data relating to patients’ pain and disability will be described with their median and interquartile range. Normally distributed numerical data will be summarised by their mean and standard deviation. In case of non-normality, median and interquartile range are presented. Examination objectives as formulated by therapists will be classified by one researcher ([name]) according to the framework of the World Health Organization’s *International Classification of Functioning, Disability and Health* (ICF)
[67] to describe patients’ functioning in terms of impairments of neuromusculoskeletal and movement-related functions, activity limitations and participation restrictions, and personal and environmental factors. Diagnostic procedures will be listed and described with their frequencies, and also outcomes of PIVM assessment, changes to the original examination objectives, diagnostic conclusions, and examiners’ level of certainty of their decision about the treatment indication will be summarised. Concordance between the formulated examination objectives concerning spinal joint motion function and the actual use of PIVM assessment will be presented as frequencies.

For each pair of therapists, 2×2 tables will be constructed and reliability for the dichotomous positive or negative decisions about whether or not SMT is indicated will be calculated as chance-corrected reliability using Cohen’s kappa
[68]. As recommended by Cicchetti and Feinstein
[69] and Byrt et al.
[70], observed agreement (%), prevalence of positive decisions (mobilisations and/or manipulations indicated) relative to the total number of indications, prevalence index (PI), bias index (BI), and specific agreement (%) in positive (p_pos_) and negative (p_neg_) decisions will be calculated in order to evaluate whether kappa was influenced by high prevalence of positive or negative decisions, or by systematic bias between examiners. PI reflects the difference between the proportion of agreement on positive indications as compared to that of negative indications. PI ranges between 0 and 1, and is high when the prevalence of concordant positive (or negative) indications is high, chance agreement is consequently also high, and kappa is reduced accordingly (prevalence effect)
[71]. BI provides a quantification of the extent to which examiners disagree on the proportions of positive (or negative) indications. BI also ranges between 0 and 1, and is high when the difference between the discordant indications is high, chance agreement is consequently low, and kappa is inflated accordingly (bias)
[71]. P_pos_ and P_neg_ are the proportions of agreement on positive and negative indications, respectively, relative to the total number of positive and negative indications, respectively, from both therapists. Overall kappa (95% CI) will be calculated as a generalized chance-corrected reliability across all pairs of therapists. See Additional file
1 for formulas.

In addition, for each pair of therapists, separate 2×2 tables will be presented for judgements about the indication for PIVM assessment and for judgements about mobility, end-feel, and pain provocation obtained from PIVM assessment (four tables in total). Observed agreement, prevalence of positive decisions, PI, BI, p_pos_, p_neg_, and overall kappa (95% CI) will also be calculated. Analyses will be conducted using DAG_Stat
[72].

Kappa (95% CI) is interpreted in accordance with value labels as assigned by Landis & Koch
[73]: <0.00: poor, 0.00-0.20: slight, 0.21-0.40: fair, 0.41-0.60: moderate, 0.61-0.80: substantial, 0.81-1.00: almost perfect. We arbitrarily assume a lower bound of the 95% CI around overall kappa of 0.60 to indicate acceptable reliability.

Univariable logistic regression analysis will be performed to explore which demographic, professional, and clinical factors contributed to the reliability of therapists’ decision-making. Firstly, patients’ demographic and clinical factors at baseline will concern their gender, age, type of complaints, duration of complaints (less or more than three months), radiation, traumatic origin, comorbidity, pain intensity, and disability. Such factors are associated with variation in diagnostic accuracy
[74], but evidence in the context of reliability is lacking. Secondly, therapists’ professional factors will include their clinical experience and weekly amount of work related to spinal disorders. Weekly amount of work related to spinal disorders was positively associated with perceived importance and confidence related to the use and interpretation of PIVM assessment
[20] and may, therefore, contribute to variation in diagnostic decision-making. In addition, other clinical factors will be explored involving PIVM assessment (indicated or not, and judgements on mobility, resistance, and pain provocation), the diagnostic conclusion (specific or non-specific neck or low-back pain), therapists’ level of certainty of their decision about the treatment indication, and the concordance between examination objectives and the use of PIVM assessment. Factors will be entered in the model as single covariates with the concordant decisions, either positive or negative, as the dependent variable. Concordant decisions will be coded as 1 while the discordant decisions will be coded 0. Therapists’ experience and work related to spinal disorders will be entered as mean scores from each pair. A p-value <0.05 indicates a statistically significant association between a factor and a concordant decision about whether or not SMT is indicated.

With a sample size of 165, a two-sided 95% CI around kappa would extend ±0.109 from the observed value of kappa, assuming a true value of kappa of 0.70, and a prevalence of positive decisions of 50%. Consequently, each pair of examiners will be asked to include 12 patients. Multiple imputation will be used to handle records with data points missing at random. If, for any reason, data on the primary outcome measure are not available or obtainable from one or both therapists, all data from this patient will be excluded from the analysis and the pair of therapists will be asked to include a new patient. Analyses will be conducted using IBM SPSS Statistics for Windows version 22.

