**Figure 1 F1:**
[figure not shown]
**A. Design of an RCT including patients positively indicated for SMT when lower bound of 95% CI around kappa >0.60 and BI <0.10. B**. Design of an RCT including only patients positively indicated for SMT by two examiners when kappa <0.60 but p_pos_ (or p_neg_) >60%.

With respect to our second research objective, it is important to note that empirical evidence for sources of bias and variation in reliability studies is lacking contrary to studies of diagnostic accuracy
[74,93-95]. Variation arises from differences between studies, for example, in terms of demographic and disease features of study participants, characteristics of examiners, setting, or test protocol. As such, it does not lead to biased estimates of reliability, but it can limit the applicability of study results
[94]. Knowledge of factors that explain variation in reliability may inform ways to improve reliability. For instance, examiner training and choosing a group of more heterogeneous study participants have been mentioned as improvement strategies, but both have their limitations and lack supporting evidence
[24]. Systematic reviews may reveal subgroups of participants, examiners, or tests that consistently show higher or lower reliability. In systematic reviews, between-study comparisons are conducted to search for these subgroups as sources of variation. However, these comparisons are less valid as they are hampered by the often strong clinical and methodological heterogeneity between studies
[96]. In addition, the identification of these sources of variation becomes even more troublesome when reliability is consistently low (or high) across studies. Within-study comparisons are the preferred method to explore variation in reliability. To date, very few studies have been undertaken in the field of manual therapy with this aim and method. Cook et al.
[97] investigated factors related to the large variability of forces used during passive accessory intervertebral movements and they found that examiners’ age, gender, experience, background and education, and frequency of use did not contribute to this variation. We present simple logistic regression analysis of concordant decisions as a flexible method that can easily be incorporated in any reliability study to explore and explain variation in reliability from a large number of demographic, professional, and clinical factors.

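### Therapist experience and spinal workload take at most 14 pair values but are tested as if about 165 patients were independent, so p<0.05 is too lenient for these two factors if agreement varies between pairs

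*Protocol article*

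**What the plan says.** The Statistical analysis section defines one outcome per patient: "Concordant decisions will be coded as 1 while the discordant decisions will be coded 0". It then fixes the model: "Factors will be entered in the model as single covariates with the concordant decisions, either positive or negative, as the dependent variable". For the two professional factors it adds: "Therapists’ experience and work related to spinal disorders will be entered as mean scores from each pair". The decision rule is: "A p-value <0.05 indicates a statistically significant association between a factor and a concordant decision about whether or not SMT is indicated".

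The Examiners section sets the number of clusters: "14 pairs of manual therapists will be invited to participate", each pair working in one practice. The Statistical analysis section sets the cluster size: "each pair of examiners will be asked to include 12 patients".

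The Discussion (text after Figure 1) confirms that an ordinary model is meant: "We present simple logistic regression analysis of concordant decisions as a flexible method that can easily be incorporated in any reliability study".

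The article mentions no random effect, estimating equation, cluster-robust variance or pair-level analysis. The section on limitations does not mention that patients are nested in pairs.

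**The concern.** A factor that is constant within a pair carries information only through differences between pairs. With 14 pairs there are 14 independent pieces of information on experience and on workload, however many patients each pair examines. A logistic regression with that factor as its only term takes its standard error from about 165 patients. The standard error is right only if two patients of the same pair are no more alike in concordance than two patients of different pairs, once the factor is accounted for.

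The plan gives reasons to doubt this. It suggests that workload may contribute to variation in decision-making. It says that working in the same practice may inflate reliability, and it aims to pair therapists of different experience. It therefore expects influences at pair level, but its test allows for none beyond the single covariate.

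At stake is whether a significant result for experience or workload can be read at the stated 5% level. The Discussion hopes that such factors will inform ways to improve reliability, and it offers the method to other reliability studies.

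**Working it through.** **Inputs from the article.** 14 pairs; 12 patients per pair (14 × 12 = 168, against a planned total of 165); true kappa 0.70; prevalence of positive decisions 50%; threshold p<0.05, taken as two-sided.

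**Input not in the article.** The ICC of concordance within pairs. It is assumed and shown over 0 to 0.20.

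**1. The plan's own figure.** At 50% prevalence and no bias, chance agreement is 0.5, so kappa = 2·p_o − 1 and SE = √((1 − kappa²)/N). The half-width is 1.96 × √((1 − 0.49)/165) = 1.96 × 0.0556 = 0.109, which matches the stated ±0.109. This concerns kappa. The article gives no error rate or power for the regressions.

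**2. Implied agreement.** p_o = (1 + 0.70)/2 = 0.85, so about 0.15 × 165 ≈ 25 discordant patients are expected.

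**3. Analytic size for a pair-constant factor.** The design effect is D = 1 + (12 − 1) × ICC. The naive variance is too small by the factor D, so the true type I error is about 2 × [1 − Φ(1.96/√D)].

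**4. Simulation.** 4,000 runs per setting; 14 pairs × 12; beta-binomial concordance with mean 0.85; null covariate; ordinary logistic Wald test at 5%. The Monte Carlo standard error near 5% is √(0.05 × 0.95/4000) ≈ 0.3 percentage points.

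| Assumed ICC | D | 168/D | Pair-constant factor, analytic | Pair-constant factor, simulated | Evenly spread patient factor, simulated | Pair-level regression (12 df), simulated |
|---|---|---|---|---|---|---|
| 0 | 1.00 | 168 | 5.0% | 4.3% | 4.8% | 5.0% |
| 0.02 | 1.22 | 138 | 7.6% | 7.0% | 4.9% | 5.4% |
| 0.05 | 1.55 | 108 | 11.5% | 10.6% | 4.6% | 4.6% |
| 0.10 | 2.10 | 80 | 17.6% | 16.6% | 5.1% | 5.4% |
| 0.20 | 3.20 | 53 | 27.3% | 25.9% | 4.2% | 5.4% |

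Two further simulations of the pair-constant factor agree. One used a random pair intercept on the logit scale and gave 5.1% with no pair effect, then 6.9%, 10.8%, 14.3% and 17.8% at ICCs of about 0.02, 0.045, 0.077 and 0.117. The other gave 5.2%, 7.2%, 9.9% and 17.3% at ICCs of 0, 0.02, 0.05 and 0.10. Repeating the tabulated simulation at mean agreement 0.75 gave similar results.

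**5. Factors that cluster only partly by pair.** With a covariate ICC of 0.2 to 0.5 (assumed), the naive test rejected 6.5 to 8.2% at outcome ICC 0.05 and 6.6 to 10.8% at 0.10. As a check, D ≈ 1 + 11 × ICC(covariate) × ICC(outcome). For 0.5 and 0.10 this is 1 + 11 × 0.05 = 1.55, which by step 3 gives 11.5%, close to the simulated 10.8%.

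**6. Candidate remedies for a pair-constant factor.** A cluster-robust Wald test on t(12) still rejected 8 to 9%. GEE with uncorrected robust variance rejected 12 to 14%. Exchangeable GEE with bias-corrected variance and t on 12 df rejected 3.5 to 5.7% at ICC 0 to 0.10 (600 runs per setting, so less precise).

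**The case against.** The strongest reply is about scope. The plan lists 18 factors: 9 patient factors, 2 therapist factors and 7 other clinical factors. Only the two therapist factors are constant within a pair. A reader might infer that every regression rejects too often. The documents and the check do not support that, because a patient factor spread evenly over pairs keeps its 5% level at every ICC tried.

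A reader might also take the correlation as certain. It is not: no ICC is given, and at ICC 0 nothing is wrong.

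Nor does it follow that spurious therapist findings are likely. If the two tests were independent, the chance of at least one false positive would be 1 − 0.93² = 14% at 7% each, or 1 − 0.83² = 31% at 17% each, against 1 − 0.95² = 10% at the nominal level. The risk is raised, but false findings are not the expected result.

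The analysis is also secondary and exploratory. The rule for the follow-on trial uses only the lower limit of kappa, the bias index and the specific agreements, so neither it nor the primary kappa depends on these regressions.

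These points limit the concern but do not remove it. Exploratory status does not change what a stated 5% threshold means. An article may leave detail to a fuller plan, but here it fixes the covariate structure, the pair-mean coding and the significance rule itself.

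**Conclusion.** The point holds for experience and weekly spinal workload, on condition that concordance varies between pairs beyond what the tested factor explains. The actual type I error is then about 7% at ICC 0.02, 10 to 11% at 0.05 and 17% at 0.10. These figures assume 14 equal pairs of 12 and 85% agreement; the ICCs are assumptions.

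For clinical factors that may cluster by therapist or practice, such as use of passive intervertebral motion (PIVM) assessment, certainty or diagnostic conclusion, the excess is smaller. It is about 6.5 to 11% at outcome ICCs of 0.05 to 0.10, and it depends on a second assumption about how strongly the factor clusters.

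The change is worth making because a valid test exists on the same data. It is not critical to the study's main conclusion.

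**What to change.** Test experience and workload at pair level: regress the 14 pair agreement proportions on the pair mean and refer the slope to t on 12 df. For clinical factors that may cluster by pair, fit a model with the pair as cluster and a small-sample-corrected variance, for example exchangeable GEE with bias-corrected variance and a t reference. Uncorrected robust GEE should not be used with 14 clusters. Patient factors spread evenly over pairs can stay as planned.

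No new data are needed. The costs are wider intervals for the therapist factors and, in the pair-level test, an effect expressed as a difference in agreement proportion instead of an odds ratio. Whether the named software offers the corrected variance should be checked; the pair-level test is an ordinary linear regression. The corrected GEE was checked for pair-constant factors, not for partly clustered ones, so a short simulation before adopting it there would be sensible.

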## Abstract

**Background:**

Manual spinal joint mobilisations and manipulations are widely used treatments in patients with neck and low-back pain. Inter-examiner reliability of passive intervertebral motion assessment of the cervical and lumbar spine, perceived as important for indicating these interventions, is poor within a univariable approach. The diagnostic process as a whole in daily practice in manual therapy has a multivariable character, however, in which the use and interpretation of passive intervertebral motion assessment depend on earlier results from the diagnostic process. To date, the inter-examiner reliability among manual therapists of a multivariable diagnostic decision-making process in patients with neck or low-back pain is unknown.

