## Background

Neck and low-back pain are common and costly disorders in adult general populations
[1-6]. Manual spinal joint mobilisations and manipulations are widely used treatments in patients with these complaints
[7,8]. Although the underlying mechanisms of these treatments are far from understood, spinal joint mobilisations and manipulations are effective as well as cost-effective in patients with non-specific neck and low-back pain although no more effective than other treatment modalities
[9-14].

Traditionally, manual therapy has a strong focus on the diagnostics, treatment, and evaluation of spinal joint function by emphasising the use of passive physiological and accessory movements
[15-17]. Passive intervertebral motion (PIVM) assessment is used to judge the quantity and quality of functions of spinal motion segments and is assumed to play an important role in diagnostically classifying patients and selecting treatment
[18]. Dutch, New Zealand, and USA manual therapists indeed believe that passive spinal mobility testing is important for deciding on manual mobilisation or manipulation as a treatment option
[19,20]. Moreover, a recent international, multidisciplinary survey showed that PIVM assessment is the most commonly used impairment outcome measure in patients with neck pain
[21].

In order to yield accurate and uniform decisions about treatment options for patients, test results need to be reliable
[22]. Reliability is a component of reproducibility along with agreement and reflects the extent to which test results can diagnostically discriminate between patients despite measurement errors
[23,24]. Agreement, on the other hand, concerns the possibility of examiners to obtain the same test results on different measurement occasions
[25]. Systematic reviews have consistently shown poor inter-examiner reliability for spinal physical tests, and for PIVM assessment in particular
[26-30]. However, the large majority of studies investigating the reliability of physical tests and PIVM assessment can be regarded as test research following a single-test or univariable approach, thus neglecting the multivariable character of the diagnostic process as opposed to diagnostic research
[31].

Physiotherapists conduct a diagnostic process by collecting data through interview and physical examination and by generating hypotheses as to why a problem exists in order to reach a decision about appropriate patient management

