[32,33]. During this diagnostic process, manual therapists indeed seem to apply, amongst others, a hypothetico-deductive way of clinical reasoning
[34,35]. PIVM assessment is usually conducted after history-taking, questionnaires, and other physical tests and is indicated after interpreting earlier clinical information and formulating specific hypotheses about spinal joint dysfunction
[35]. Moreover, Canadian manual therapists reported to decide on manual mobilisation or manipulation based on their whole clinical assessment and clinical reasoning in a patient
[36]. It is therefore reasonable to assume that the diagnostic process in manual therapy has a multivariable character.

Over the last three decades, many systems have been developed for classifying patients with spinal disorders, in particular for those with low-back pain
[37]. A systematic review found 28 systems for classifying chronic low-back pain alone and it was concluded that there was insufficient evidence to support or recommend any particular system for use in clinical description, determining prognosis, or predicting response to treatment
[38]. Some systems were tested for their inter-examiner reliability, but evidence was either conflicting or moderate to strong for poor reliability
[27]. On the other hand, using clusters of tests for diagnosing sacroiliac joint dysfunction yielded acceptable reliability
[39-41]. However, the majority of these systems either lack evidence for their reliability, only use certain parts of the clinical examination (e.g. only physical tests), are prescriptive in their application, do not include PIVM assessment, are not related to manual therapy interventions, or do not direct towards treatment decisions. Some systems
[42,43] were developed as treatment-based classification algorithms for subgrouping patients with low-back pain and were strongly based on factors derived from several clinical prediction rules
[44-47]. However, these rules lack validation, and methodological and statistical issues regarding their development have been raised
[48]. In contrast to the field of classification systems for low-back pain, the development and number of systems for classifying neck pain patients lie far behind. Besides a treatment-based classification system for physiotherapy interventions

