[49], clinical prediction rules have been derived to identify factors that predict response to spinal manipulation in patients with neck pain but with identical problems as in the rules for low-back pain as mentioned above
[50-55]. In a systematic review, Gemmell and Miller
[56] found poor inter-examiner reliability of multitest regimens using only physical tests for identifying manipulable spinal lesions in chiropractic. Including pain scores and medical history next to manual examination of spinal motion segments resulted in high accuracy in identifying neck pain patients
[57]. To summarise, however, the value of the diagnostic process as a whole to classify patients with neck or low-back pain in order to decide whether or not spinal mobilisations or manipulations are indicated remains unclear.

This is the protocol of a study that aims to determine the inter-examiner reliability among Dutch manual therapists of indicating spinal joint mobilisations or manipulations in patients with neck or low-back pain based on a multivariable, hypothesis-based diagnostic reasoning and decision-making process. Secondly, using univariable logistic regression analysis of concordant decisions about indications, we will explore which demographic, professional, and clinical factors can explain variation in reliability of therapists’ decisions with specific attention to the contribution of PIVM assessment.

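### PIVM's contribution to agreement is estimated only by crude single-covariate regression, so its odds ratio is open to confounding by the findings that prompted PIVM

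*Protocol article*

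**What the plan says.** The aims at the end of the Background include explaining variation in reliability "with specific attention to the contribution of PIVM assessment". The Statistical analysis section sets the method: "Univariable logistic regression analysis will be performed to explore which demographic, professional, and clinical factors contributed to the reliability of therapists’ decision-making". Each factor stands alone: "Factors will be entered in the model as single covariates with the concordant decisions, either positive or negative, as the dependent variable". The outcome is binary: "Concordant decisions will be coded as 1 while the discordant decisions will be coded 0". The PIVM covariates are described thus: "other clinical factors will be explored involving PIVM assessment (indicated or not, and judgements on mobility, resistance, and pain provocation". No adjusted model appears in the Abstract, the aims, the Statistical analysis section or the Discussion.

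The article also describes how PIVM comes to be used. The Abstract says that "the use and interpretation of passive intervertebral motion assessment depend on earlier results from the diagnostic process", and the Background says that "PIVM assessment is usually conducted after history-taking, questionnaires, and other physical tests and is indicated after interpreting earlier clinical information". Under Procedures, baseline data reach each therapist before the examination, history-taking and the setting of objectives follow, and PIVM is done only where the therapist considers it indicated.

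The Statistical analysis section lists type and duration of complaints, radiation, traumatic origin, comorbidity, pain and disability as candidate determinants of concordance, each to be tested on its own.

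**The concern.** A feature that influences both whether PIVM is used and whether two therapists agree can produce a PIVM association without any PIVM effect, or hide a real one. By its own account the plan has the first link, since earlier findings lead to PIVM. It treats the second link, from clinical features to concordance, as a possibility worth testing. Single-covariate models cannot separate PIVM from the clinical picture that prompted it.

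At stake is the reading of the second objective. The plan applies a p<0.05 rule to each factor, speaks of factors that contribute to or explain reliability, and in the Discussion recommends the method for other reliability studies and says that such knowledge may help improve reliability. A reader could take a significant PIVM odds ratio as evidence that using PIVM changes agreement. The limitations section does not warn that the PIVM estimates are unadjusted.

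**Working it through.** **1. The plan's own figure.** Inputs from the Statistical analysis section: N = 165, kappa 0.70, prevalence 50%. At 50% prevalence the variance of kappa is (1 − κ²)/N, so the half-width is 1.96 × √((1 − 0.49)/165) = 0.109. The stated ±0.109 reproduces, and this point does not touch it.

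**2. Expected discordant decisions.** Chance agreement at 50% prevalence is 0.50. Observed agreement is 0.50 + 0.70 × 0.50 = 0.85. Discordant decisions: 0.15 × 165 = 24.75, about 25. With kappa 0.50 the count is about 41; with kappa 0.80 it is about 16.

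**3. How large could the distortion be?** The documents give no figures for PIVM use by clinical picture, or for the link between picture and concordance. The following are therefore assumptions:
- PIVM is treated as one yes/no value per patient.
- A binary clinical picture is present in half of the patients.
- Overall concordance is 85%.
- PIVM has no effect within either level of the picture.

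Let a₁ and a₀ be the proportions receiving PIVM with and without the picture, and q₁ and q₀ the concordance in those groups. Then:
- concordance with PIVM: c₁ = (a₁q₁ + a₀q₀)/(a₁ + a₀)
- concordance without PIVM: c₀ = [(1 − a₁)q₁ + (1 − a₀)q₀]/(2 − a₁ − a₀)
- crude odds ratio = [c₁/(1 − c₁)] / [c₀/(1 − c₀)]

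Worked case: a₁ = 0.80, a₀ = 0.40, and an odds ratio of 4 between picture and concordance, which gives q₁ = 0.930 and q₀ = 0.770. Then c₁ = (0.744 + 0.308)/1.20 = 0.877 and c₀ = (0.186 + 0.462)/0.80 = 0.810. The crude odds ratio is 1.67, where the true value within each group is 1.00.

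Crude PIVM odds ratio with no PIVM effect:

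| PIVM use with / without the picture | Picture–concordance OR 0.25 | 0.5 | 1 | 2 | 4 |
|---|---|---|---|---|---|
| 60% / 40% | 0.776 | 0.873 | 1.000 | 1.145 | 1.288 |
| 80% / 40% | 0.574 | 0.749 | 1.000 | 1.320 | 1.671 |
| 90% / 30% | 0.420 | 0.644 | 1.000 | 1.513 | 2.159 |

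A stronger input gives a further case. With concordance of 95% versus 75% (odds ratio 19/3 = 6.3) and PIVM use of 80% versus 40%, c₁ = (0.76 + 0.30)/1.20 = 0.883 and c₀ = (0.19 + 0.45)/0.80 = 0.800, so the crude odds ratio is 1.89.

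**4. Chance of a misleading p<0.05.** By a Wald approximation that ignores clustering within pairs, the nominal 5% becomes about 6% to 22% in the first two rows where the picture matters, and about 16% to 41% in the third row. In the 1.89 case the standard error of the log odds ratio is 0.44. The expected 95% interval is about 0.80 to 4.5, and the chance of p<0.05 is about 31%.

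**5. Room for adjustment.** PIVM plus two or three one-parameter covariates makes three or four parameters. With 24.75 discordant decisions that is 8.3 or 6.2 events per parameter. At kappa 0.80, four parameters leave 16.5/4 = 4.1. A small, penalised model is feasible; a large one is not.

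**The case against.** The best defence is that the analysis is declared exploratory and its decision rule speaks of association. A crude odds ratio validly estimates a crude association. With about 25 discordant decisions, single-covariate models are a defensible choice. In the illustrations sampling error is large: even at an odds ratio of 1.89 the interval would span 1. All of this stands and limits the weight of the point.

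Three stronger readings are tempting, and the documents do not support them.
- A reader might infer that the plan contradicts itself, because the Background faults earlier work for "thus neglecting the multivariable character of the diagnostic process as opposed to diagnostic research". That criticism concerns studies of the reliability of a single test in isolation. The plan answers it with its primary outcome, which is agreement on a decision reached after the whole diagnostic process. It does not require correlates of agreement to be mutually adjusted.
- A reader might infer that the PIVM odds ratio is in fact confounded. That requires earlier findings to be related to concordance, and the Statistical analysis section itself says that evidence on such factors is lacking for reliability. If they are unrelated, the crude value is 1.00.
- A reader might infer that conclusions should rest on an adjusted estimate alone. A few baseline items cover only part of what history-taking reveals, so an adjusted figure could look cleaner than it is.

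What the objection does not remove is the gap between a crude association and the wording about contribution and explanation.

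**Conclusion.** The point holds in limited form. The PIVM odds ratio is open to confounding of unknown size and direction, and on its own it cannot support statements about what PIVM contributes to agreement. Under the assumed inputs with no true effect, moderate scenarios (PIVM use of 60% or 80% versus 40%, odds ratio 2 to 4 between picture and concordance) give about 1.15 to 1.67. Stronger scenarios give about 1.9 to 2.2, and the opposite direction reaches about 0.4. These sizes rest on assumed values and show only what could happen.

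This is not a detail left to a fuller document: the article commits to single covariates. It affects only the interpretation of an exploratory secondary objective. The kappa estimate, its precision and the thresholds in the Discussion for future trial designs are untouched. It is a cheap improvement.

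**What to change.** - Beside the crude estimate for PIVM indicated or not, prespecify one adjusted model with two or three baseline factors already collected, for example type of complaint, duration (less or more than three months) and radiation.
- Fit it by penalised (Firth) logistic regression, because of the small number of discordant decisions. Firth reduces small-sample bias but adds no information.
- Report the crude and adjusted estimates together with their intervals, so that a reader can see whether the association moves.
- Describe the crude PIVM odds ratios, including those for mobility, resistance and pain provocation, as associations and not as PIVM's contribution.
- State in the limitations that confounding by history findings outside the model remains.

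The cost is a few extra model fits on existing data, possibly in other software, and somewhat wider adjusted intervals. No new data are needed.
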